### 4.4 Sample size calculation

In order to estimate whether an ultra-low daily dose of artificial UVB (~0.5 SED) complying to the photobiological safety requirements for general lighting could be effective in raising serum 25(OH)D,

simulations based upon Diffey's model were conducted [42]. The simulation results indicate that when the foreseen intervention dose (0.45 SED) is applied in the optimal conditions (evenly over 8 hours and 20 minutes and 10.5 % body surface area exposure), a maintenance of summer serum vitamin D3 levels could be realized. Figure 2 represents the simulation (Exposure: 0.45 SED; Body Surface Area (BSA): 10.5%, front face (3.5%), 2 x back lower arms (3%), 2 x backside hand (3%), neck (1%)) as well as the effect of such an intervention in the foreseen study timespan of eight weeks. For the study it is expected that at optimized conditions a difference of about 17.6 nmol/L between intervention and control group can be realized in those 8 weeks. Having said that, the expected variance in actual exposure each day will be larger based upon the analysis of variations in exposure duration (desk occupancy) and body surface area exposure. The estimated impact of exposure to a minimum 0.225 SED and a body surface area % minimum of 6.5%) on serum vitamin D3 levels are depicted in Table 2.

[figure not shown]

**Figure 2:** Simulations results conducted to estimate the impact of a 8 week UVB exposure of office workers with input parameters (10.5% skin exposure: front face (3.5%), 2 x back lower arms (3%), 2 x backside hand (3%), neck (1%)). At start: 66.4 nmol/L; End intervention group: 61.7 nmol/L (- 4.7 nmol/L); End Control Group: 44.1 nmol/L (-22.3 nmol/L); Expected intervention effectiveness: +17.6 nmol/L. The UVB dose is evenly (UVI=0.06) given over a period of 8 hours and 20 minutes during the workday. This figure is based on exposure during 5 working days.

**Table 2:** Simulation results for expected serum vitamin D3 levels at reduced body surface area (BSA%) exposure and intervention dose (0.225 SED (50%)).

|                             |                                       | Estimated Serum VitD Intervention Effect (nmol/L) compared to control group |                      |                                              |

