A sample size calculation using Gpower was performed assuming that the intervention will reach a (conservative) difference of 8.8 nmol/L between the intervention and the control group (situation 3 in Table 2) at the final measurement point (at 8 weeks). This would mean that the decrease in the control group from baseline to week 8 would be -22.3 while in the intervention group this would be -13.5 (difference of 8.8 nmol/L). The sample size calculation is based on the statistical analysis conducted for the primary objective, namely the difference in serum 25(OH)D between the intervention and control group at the final measurement point, taking into account an alpha of 0.05 and a power of 0.90. The standard deviation within one group is estimated based on a previous similar study which also implemented low-dose UVB exposure to increase serum 25(OH)D in a sample of 20 healthy participants, albeit over a week period using three full-body UVB sunbed sessions [35]. In the post-measurement of this study, they found a significant increase in serum 25(OH)D of 13.9 nmol/L. One month after the end of the UVB intervention they still found a significant increase of 8.8 nmol/L, which is a similar difference we expect in the intervention group compared to the control group. The standard deviation for the power calculation was therefore based on the standard deviation on the difference score found in the sample in this study (similar sample size and similar changes in serum 25(OH)D), namely 8.4 nmol/L. The sample size for detecting a difference of 8.8 nmol/L assuming a standard deviation of 8.4 nmol/L in each group would be 17 participants in each group (see figure 3 below). As we currently only have the availability of 14 lamps, we will choose for 14 participants in each group, and aim to find a larger effect, which is not unlikely when on average, there is somewhat more than 50% desk occupancy and/or if we reach a higher exposure surface area.

[figure not shown]

**Figure 3.** Sample size calculation for change in serum 25(OH)D at 8 weeks

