## 7.2 Randomisation, blinding and treatment allocation

For a full visual overview of the allocation procedure see Figure 6. The independent agency CG selections will make a selection of eligible participants based in the in- and exclusion criteria (see sections 4.2 and 4.3). A list with eligible participants who are interested in participating in the study is mailed to the responsible researcher at the TU/e who will perform block randomization for assignment to the conditions. However, in case insufficient participants are available who work at least 2.5 days at their home office, selection for the intervention group will then be based on presence at the desk (at least 50%). This selection is believed not to influence the primary outcome parameter (25(OH)D serum levels) and as such the conclusions around the primary objective: Participants will not receive any (noteworthy, see [39]) UVB exposure (that could influence the serum 25(OH)D) unless they are allocated to the intervention group. In the statistical analysis, care will be taken to control for potential group differences in desk presence, time spent outside and vitamin D intake by food.

[figure not shown]

**Figure 6.** Allocation procedure

In addition to randomization, blinding is frequently applied to prevent that participants know they are in the control or intervention group. For this specific pilot, only 14 luminaires are available. These luminaires will be placed at the side of the participant's desk when allocated to the experimental group. As such the participant is aware that he or she will receive UVB. Blinding by reducing the sample size to 14 instead of 28 has been considered. However, to prevent that the data can be allocated (identified) to individual persons and to have sufficient power in the study, the total number of participants is estimated to be >25 in total. Since the 25(OH)D levels will not be affected by a pseudo-randomization and non-blinding strategy, it has been chosen to secure privacy of the participants and prioritize a sufficient sample size, and blinding is compromised.

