### **Secondary objective**

The secondary objectives focusing on sleep and general feelings of fatigue on the other hand can be influenced by prior knowledge to allocation to the intervention and control. Therefore, we will include these for exploratory purposes and we will only explore whether variation in vitamin D status in both groups correlates with variations in sleep and general feelings of fatigue, instead of investigating the direct effect of the intervention in these indicators.

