After that, an explorative Linear Mixed Model (LMM) analysis will be conducted to examine changes in serum 25(OH)D over time (i.e., first and second measurement, using baseline scores as a control variable). LMM analyses will be executed because this type of analysis takes into account dependency of the data due to the repeated measures as well as potential missing values at any of the measurement points. In case a significant Intervention \* Measurement interaction is found ( $p < 0.05$ ), post-hoc comparisons are conducted to investigate differences between the intervention and control group at each of the two measurement points. In addition, we will conduct an exploratory LMM analysis in which we investigate the correlation between UVB dose (calculated based on desk presence and clothing) and serum 25(OH)D over time to examine whether there are large differences in these values based on the UVB dose participants received. These explorative analyses will also be controlled for time spent outside during daytime.

Last, exploratory LMM analyses will be conducted to investigate relations between the variation in serum 25(OH)D and variations in sleep duration, sleep quality, and general feelings of fatigue.

This will be established by running a LMM model with serum 25(OH)D as well as measurement point as predictor in order to account for changes in sleep patterns or fatigue levels over time. For visual inspection purposes, this will also be investigated separately in both the intervention and the control

group. This will be analyzed in this way due to a lack of blinding in participants which may create bias when directly investigating the effect of the intervention on fatigue/sleep.

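### The sleep and fatigue mixed model has no arm term, so the unblinded arm contrast it is meant to avoid re-enters through 25(OH)D

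*Protocol*

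**What the plan says.** Section 7.2 states that the trial is not blinded: "As such the participant is aware that he or she will receive UVB". Under its Secondary objective heading, it accepts that sleep and fatigue "can be influenced by prior knowledge to allocation to the intervention and control". It therefore plans only to correlate vitamin D status with these outcomes, "instead of investigating the direct effect of the intervention in these indicators".

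Section 9 implements this by "running a LMM model with serum 25(OH)D as well as measurement point as predictor". Arm is not among the named predictors. A by-arm analysis follows, with a restricted role: "For visual inspection purposes, this will also be investigated separately in both the intervention and the control" group. The reason given for analysing the data this way is "due to a lack of blinding in participants which may create bias when directly investigating the effect of the intervention on fatigue/sleep".

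Section 4.4 gives the expected effect of the lamp on the predictor. Under optimised conditions, "a difference of about 17.6 nmol/L between intervention and control group can be realized in those 8 weeks". The sample size uses a more cautious 8.8 nmol/L, with an SD of 8.4 nmol/L for the change.

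**The concern.** Replacing arm with 25(OH)D removes the arm contrast only if the two are unrelated. Here the intervention is designed to make them related. With no arm term, anything that shifts the lamp arm's self-reports after baseline is partly absorbed by the 25(OH)D slope. Measurement point cannot absorb it, because both arms share the same visits.

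Expectation is one such shift. Another is visible light: the luminaire delivers white light together with UVB (section 6.2), controls receive no lamp (section 3), and section 1 itself links daytime light to sleep quality and daytime functioning. Under the fallback allocation in section 7.4, arm is assigned by desk presence and consent timing rather than at random, which adds a further possible arm difference.

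The result at risk is the stated secondary objective (section 2.2). Section 11.6 considers publishing the correlational data, and section 1 envisages a larger study of sleep and fatigue based on the pilot's results. A placebo or white-light effect could be carried forward as a vitamin D association.

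**Working it through.** The protocol gives no figure for this analysis, so there is none to reproduce.

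**Inputs from section 4.4.** Arm difference in 25(OH)D of 6.2 nmol/L at week 4 and 8.8 at week 8 (cautious case), or 12.4 and 17.6 (optimal case); SD of change 8.4; 14 per arm; three visits.

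**Assumptions not in the protocol.** An expectation shift of 0, 0.5 or 0.8 SD in the lamp arm after baseline; between-person SD of 25(OH)D of 10 or 20 nmol/L; outcome intraclass correlation 0.6; control-arm week-4 mean at 55% of the 8-week decline; no true effect of 25(OH)D on the outcome.

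**Step 1: how far the predictor marks the arm.** With equal arms, the share of week-8 *change* variance due to arm is (D/2)² / ((D/2)² + 8.4²).
- D = 8.8: 19.36 / (19.36 + 70.56) = 0.215, or 22%.
- D = 17.6: 77.44 / (77.44 + 70.56) = 0.523, or 52%.

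The predictor as worded is the *level*. With a baseline SD of 20 and change independent of baseline, the shares are smaller:
- D = 8.8: 19.36 / (19.36 + 400 + 70.56) = 4%.
- D = 17.6: 77.44 / (77.44 + 400 + 70.56) = 14%.

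**Step 2: the false slope in closed form, on change scores.** A shift δ in the lamp arm gives a slope of (δD/4) / ((D/2)² + 8.4²). With δ = 0.5 SD:
- D = 8.8: 1.1 / 89.92 = 0.0122 per nmol/L, or 0.12 SD per 10 nmol/L.
- D = 17.6: 2.2 / 148 = 0.0149 per nmol/L, or 0.15 SD per 10 nmol/L.

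The slope is zero only if δ = 0 or D = 0. A random-intercept model on levels also uses stable differences between people, which dilutes this slope, so the planned model itself was simulated.

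**Step 3: simulation.** Random-intercept model fitted by profile REML, 1,000 trials per row, significance taken as |slope/SE| > 2.0. Slopes are in outcome SD per 10 nmol/L; percentages are false-positive rates.

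| Separation, weeks 4/8 | Between-person SD | Shift (SD) | Planned model | With arm and arm × measurement |
|---|---|---|---|---|
| 6.2/8.8 | 10 | 0 | −0.003; 6.3% | −0.003; 6.4% |
| 6.2/8.8 | 10 | 0.5 | 0.065; 10.4% | 0.004; 6.0% |
| 6.2/8.8 | 10 | 0.8 | 0.096; 15.9% | −0.002; 5.8% |
| 6.2/8.8 | 20 | 0 | 0.001; 6.2% | 0.001; 5.6% |
| 6.2/8.8 | 20 | 0.5 | 0.030; 9.4% | 0.001; 6.8% |
| 6.2/8.8 | 20 | 0.8 | 0.048; 10.3% | 0.001; 4.5% |
| 12.4/17.6 | 10 | 0 | 0.000; 6.6% | −0.001; 6.3% |
| 12.4/17.6 | 10 | 0.5 | 0.093; 16.8% | −0.002; 5.9% |
| 12.4/17.6 | 10 | 0.8 | 0.147; 35.0% | −0.008; 7.2% |
| 12.4/17.6 | 20 | 0 | −0.001; 5.7% | 0.001; 5.4% |
| 12.4/17.6 | 20 | 0.5 | 0.050; 11.9% | 0.001; 5.1% |
| 12.4/17.6 | 20 | 0.8 | 0.080; 21.1% | −0.002; 5.8% |

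The Monte Carlo standard error is about 0.7 percentage points at a 5% rate (√(0.05 × 0.95 / 1000)) and 1.2 points at 17%.

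A model fitted in the control arm alone shows no bias: slopes within 0.011 of zero and rates of 5.1 to 7.8%.

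Further simulations of the same structure at a 0.5 SD shift agree: about 8 to 10% at 8.8 nmol/L and 11 to 21% at 17.6 for the planned model, and 4 to 6% after adjustment. Replacing the level with a within-person 25(OH)D term, still without arm, does not help: the rate is 11 to 19% (3,000 trials per scenario, baseline SD 20).

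**The case against.** The strongest reply is that a within-arm analysis is already planned and is free of this bias. The sentence about lack of blinding comes directly after it, and section 7.2 speaks of vitamin D variation in both groups, so the by-arm step may be part of the intended protection. This softens the point: the defect lies in which estimate leads. It does not remove it, because section 9 gives the by-arm step a visual role and leaves the pooled slope as the estimate.

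Second, the predictor list may not be complete, and covariates of an exploratory model can be settled in an analysis plan. Section 9 does omit dietary vitamin D, which section 7.2 promises to control for. But here the protocol names the predictors and gives a rationale that those predictors do not meet. That is a flaw in what is written, not a detail left for later.

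Third, the 22% and 52% shares describe change scores; for levels they are 4% and 14% under the stated assumption. This is correct, and neither set measures the bias in a random-intercept model. The size therefore rests on the simulation.

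Fourth, at the design value of 8.8 nmol/L with a 0.5 SD shift the inflation is moderate, the analysis is exploratory, and no significance level is clearly set for it. All of this stands and limits the weight of the point. The false slope, however, does not depend on any significance criterion.

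Finally, arm adjustment discards the only experimentally induced variation in 25(OH)D. That is true, but it is the same contrast that sections 7.2 and 9 decline to interpret without blinding.

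**Conclusion.** The concern holds. As written, the pooled model does not deliver the protection from unblinded reporting that the protocol gives as its reason. With an assumed 0.5 SD expectation shift and no true 25(OH)D effect, the planned model yields a false slope of 0.030 to 0.065 SD per 10 nmol/L at the cautious separation and 0.050 to 0.093 at the optimal one. The false-positive rates are 9.4 to 10.4% and 11.9 to 16.8%. With a 0.8 SD shift they reach 10.3 to 15.9% and 21.1 to 35.0%.

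These sizes depend on the assumed shift, between-person SD and outcome correlation. The mechanism does not: the bias vanishes only if the lamp arm's self-reports do not shift or the lamp does not separate the arms on 25(OH)D. The analysis is exploratory and the primary endpoint is untouched, so this is a correction that should be made rather than a threat to the trial's main conclusion.

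**What to change.** In section 9, specify arm and arm × measurement point as fixed effects in every sleep and fatigue mixed model, alongside 25(OH)D and measurement point. Name the resulting within-arm 25(OH)D slope as the reported estimate and keep the separate by-arm analyses as support. If the by-arm analysis was always meant to carry the conclusion, say so explicitly.

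The cost is one line of text and up to 3 degrees of freedom (1 for arm, 2 for arm × measurement point), plus the loss of the arm-driven part of the 25(OH)D variation. The adjusted slope remains observational. Within the lamp arm, desk time drives both UVB and white-light exposure, so the report should describe the slope as an association.

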## **10. ETHICAL CONSIDERATIONS**

### **10.1 Regulation statement**

The study will be conducted in accordance with the principles of the Declaration of Helsinki (Amendment of the 59th WMA General Assembly, Seoul, Korea, October 2008) in accordance with the Medical Research Involving Human Subjects Act (WMO) and conform General Data Protection Regulation (GDPR) effective:25 May 2018.

### **10.2 Recruitment and consent**

The selection and recruitment will take place by a stepwise approach executed by an external party (CG selections) (see also section 7.4):

1. CG selections will send out an e-mail to the population base in Eindhoven and surroundings (18+) including the sum-up of the in- and exclusion criteria. Via an e-mail to CG selections, participants can express interest in participation in case they meet the in- and exclusion criteria. In the email from CG selections, participants also give consent to send personal information (name, phone number, home address) to TU/e.
2. CG selections will call participants who are interested in participating and double-check the criteria for participation via phone. Participants will give oral and written permission to CG selections to share their e-mail and phone number with the TU/e researcher ([name]).
3. If the employee has given permission to share the e-mail address with the TU/e, the TU/e will approach the employees and inform them on the procedure of the pilot study towards the effects of artificial UVB on vitamin D levels by e-mail. The participant will sign the consent form after receiving the oral instructions about the study and reading the participant information.
4. Eligible participants will be randomized to the intervention or the control group.

Before the start of the execution of the study protocol, participants who adhere to the inclusion criteria will be contacted and informed about the study by the TU/e researcher ([name]) and provided the opportunity to ask questions. At the end of this meeting, participants are asked to read the participant information again in their own time and send back the signed informed consent form if they decide to participate. Participants can ask any questions regarding the study via e-mail before deciding to participate. Furthermore, the researcher will emphasize that it is always possible to stop at any time during the study without the necessity to explain choices, without any further consequences. In case sufficient participants meet the in- and exclusion criteria, block randomization will be used by the

responsible researcher to assign participants to conditions. Otherwise, participants who have at least 2.5 days of desk presence at home (and meet the other criteria) will be assigned to the intervention condition first (based on timing of sending back the informed consent form) and the other participants will be assigned to the control condition.

Participants will receive the first questionnaire via an e-mail link in the morning of the first assessment day (first blood sampling). The outcome of the first blood sample will be awaited before starting the intervention (switching on the luminaire at the desk). This is done so that participants with high vitamin D levels that need medical attention ( $>375$  nmol/L, [41]) can be excluded from the study before receiving any extra UVB exposure (further increasing their vitamin D levels). Although we do not expect such high vitamin D levels, if it occurs, participants will be contacted by the responsible researcher explaining that participating is not possible due to high vitamin D levels in the first blood sampling test. Participants will also be advised to check their level again at their general practitioner to see if a medical reference is needed.

Due to the nature of the study procedure and involved parties the participant will be asked to sign three consent forms three informed consents:

1. Consent on the privacy regulations and conditions from CG selections: <https://www.cgresearch.nl/voorwaarden-en-privacy/> and permission to send personal data (name, phone number, home address) to TU/e for study participation.
2. Informed consent form for study participation (including permission to send contact details to Signify with the purpose of installation of the luminaire, and permission for DVU to share the serum vitamin D values with the research team at TU/e).
3. Written consent from Signify for receiving the luminaire and not trying to sell it / disassemble the luminaire (consent given at the installation of the luminaire)

### **10.3 Objection by minors or incapacitated subjects (if applicable)**

Not applicable.

### **10.4 Benefits and risks assessment, group relatedness**

#### **10.4.1 Benefits**

Expected benefits (particularly in intervention group) is maintenance summer vitamin D3 levels and through that an enhanced sense-of-wellbeing.

#### 10.4.2 *Possible burden*

The main burden for participation in the study will be time consumption and slight discomfort to perform the blood sampling and to fill in the online questionnaire. Expected time consumption is estimated to be around 100 minutes maximum in total during the full 8-week study period. The desk-based lighting intervention and most of the measurements will be performed at current workspaces with minor interference with normal activities. Table 3 provides an overview of the estimated time investment per measurement type. The duration in Table 3 is excluding the travel time to and from DVU (three times), which depends on the home address of the participant.

**Table 3** Overview of estimated time investment

| Frequency | Measurements         | Time       |
|-----------|----------------------|------------|
| 3x        | Online questionnaire | 10 minutes |
| 3 x       | Blood sampling       | 10 minutes |
| 40x       | Daily diary          | <1 minute  |

#### 10.4.3 *Potential risk*

While potential risks related to the lighting intervention are expected to be minimal, exposure to the personal desk-based lighting intervention may result in undesirable experiences such as experienced discomfort (e.g., visual discomfort or eyestrain) or headache. Additionally, the use of the study protocol might result in distressing effects in relation to an oversensitivity to UVB, unknown at the start of the study. In that case if the participant notices a potential distressing effect, he/she can stop immediately.

Negative effects of UVB are associated to the formation of cyclobutylpyrimidine dimers in DNA contributing to the mechanism of erythema and sunburn formation, generally occurring during prolonged exposure at very sunny days ( $UV-I > 5$ ). To place the UV dose applied in this study in context, the dose received throughout a full working day would be equivalent to 10 minutes in bright sunlight at lunchtime on a summer day in Northern Europe. It is clearly **below the daily dose for the EU Safety Directive 2006/25/EC, and well below the erythema (sunburn) threshold for all skin types**. Individuals who suffer from photosensitivity disorders, take photosensitising medication or have had treatment for skin cancer will be excluded from the trial. The main identified risk factors associated with these photobiological safety aspects:

- exceeding the 0.7 SED per day limit due to long office hours
- direct (prolonged) viewing of the UVB LED at short distances
- lack of awareness of UVB irradiance from the source

have been mitigated by design, protective measures and information for safe use.

The contribution to risk of developing skin cancer by exposure to ultra low doses of artificial UVB during a 2-month period is considered to be negligible:

- The ultra-low daily dose is five-fold lower than the guideline to prevent sunburn for skin type 1.
- The recommendation of the KWF for required healthy sun exposure is in line with what is intended in this study.
- The potential protective effects of vitamin D to attenuate inflammation due to sunburn

In summary, the application precautions are considered to make the luminaire safe for the intended application, as described in the photobiological safety photobiological hazard (European directive 2006/25/EC), and the device can be regarded safe to use under application conditions according to IEC 62471 .

